### Intervention

The intervention ‘VolleyVeilig’ (in Dutch) is made available exclusively to the participants within the intervention group, aiming to prevent or reduce the occurrence of finger/wrist, shoulder, knee and ankle injuries among adult recreational volleyball players. The intervention consists of a warm-up program including more than 50 distinct exercises (with different variations and levels) that should be conducted at least twice a week prior to any volleyball activity (training or match) [10]. The intervention is divided into 6 phases, each lasting 5 to 6 weeks (accordingly to a typical volleyball season), providing volleyball coaches every week with a new warm-up program that shows progressive increments in terms of intensity, frequency, duration and/or complexity. Each warm-up program lasts 15 min and is divided into a preparatory cardiovascular warm-up (2 to 3 min), core stability exercises (2 to 3 min; for instance straight plank), exercises principally directed towards the prevention of knee injuries (4 to 5 min; for instance squat), and exercises principally directed towards the prevention of shoulder injuries (4 to 5 min; for instance external rotation strength with resistance elastic). The exercises directed towards the prevention of ankles injuries (for instance one legged stance) are embedded within each warm-up program. All warm-up programs of the intervention are overseen by the coaches, being available through a website and an application for smartphone/tablet (automatic synchronisation) that are accessible with a username and password. Information and instructions about the exercises are available as texts and video’s (including voice-over). Illustrations of the website and application for smartphone/tablet as well as examples of exercises within the intervention are presented in Fig. 2.

**Fig. 2 Fig2:**
[figure not shown]
The intervention for volleyball players

### Volleyball as usual

The teams and players in the control group will not have access to the intervention and will be asked to perform their warming up and volleyball activities as usual.

### Exposure and injury monitoring

Coaches will be asked every two weeks during the 2017–2018 season to retrospectively report the details of their players’ participation for each training and match. Therefore, an online form sent by email will be used (anonymous and coded for privacy reasons). A reminder will be sent to coaches after approximately four days in case of no response. Once completed, the online forms will be saved automatically on an electronic server secured according to good clinical practice with forced strong passwords, Secure Sockets Layer security and regular backups.

Players will be asked every two weeks during the 2017–2018 season to complete the translated and modified Dutch version of the Oslo Sports Trauma Research Centre questionnaire (OSTRC) [11, 12]. The OSTRC questionnaire has been proposed and validated to register and monitor sports-related health problems over time, including acute and overuse injuries [13]. The internal consistency (Cronbach’s a) of the OSTRC questionnaire is estimated at 0.96 and 0.91 for overall problems (including illnesses) and overuse injuries, respectively [11, 13]. With this questionnaire, both acute and overuse injuries are registered through four key questions related to: (i) difficulties to participate normally in volleyball activity, (ii) reduced training volume due to injury or complaint, (iii) influence of injury or complaint on performances, and (iv) experienced complaint i.e. symptoms during volleyball during the previous 2 weeks. If no problems are reported on these four key questions, the questionnaire is finished. If an injury or complaint is reported, subsequent questions are asked about location, circumstances, recurrence and return to play. In the present study, acute injury is defined as a sudden event sustained by a player during a volleyball activity (training or match) that results in the player to stop his or her volleyball activity [14, 15]. Overuse injury is defined as a non-sudden event gradual in onset sustained by a player due to participation in volleyball that results in reduced performance and/or ultimately in the player to decrease or stop his or her volleyball activity (training or match) [14, 15]. For the registration of injury, an online form sent by email will be used (anonymous and coded for privacy reason). A reminder will be sent to players after approximately four days in case of no response. Once completed, the online forms will be saved automatically on an electronic server secured according to good clinical practice with forced strong passwords, SSL security and regular backups.

### Adherence

Being an important construct in effectiveness studies and referring to the degree that teams and athletes follow the prescribed intervention, adherence to VolleyVeilig will be monitored during the 2017–2018 season [16]. Therefore, the coaches allocated to the intervention group will be asked to report every two weeks for each session (training and match) and for each player whether VolleyVeilig is used and the number of VolleyVeilig exercises performed per session. These questions will be embedded in the online form used to monitor the players’ exposure. In addition to the coaches’ report, study team members will make random unannounced visits to the teams allocated to the intervention group and will observe the execution (or not) of VolleyVeilig at the beginning of a session (training or match) from a location where the coaches are unaware of this observation. To explore the warm-up activities performed in the control group, similar random unannounced visits will be conducted and observations will be made.

### Statistical analysis

Descriptive analyses (mean, standard deviation, frequency, range) will be conducted for the different baseline variables in both study groups. To evaluate the success of the randomization and matching, baseline values will be analysed for differences between the intervention and control group (Chi Square, independent T-tests and/or Mann-Whitney test). Total, training and match incidence of acute injury (and its 95% CI) will be calculated by dividing the number of newly incurred acute injuries (excluding re-injuries) identified during the follow-up by the sum of volleyball exposure (total exposure, training exposure and match exposure) in hours until the first injury [14, 15]. For overuse injuries, prevalence repeatedly measured over time is considered the preferable measure [15]. Therefore, the mean prevalence (expressed as percentage) of overuse injuries repeatedly measured over time will be calculated for each 2-week period by dividing the number of participants reporting an overuse injury during that period by the total number of respondents during the same period. Then, mean prevalence (and its 95% CI) will be calculated by dividing all prevalence rates measured every 2 weeks by the number of 2-week periods. Differences in the incidence of acute injury between the intervention and control groups will be assessed using cox regression analysis (significance level set at *p* < .05; adjusted for age and/or gender). Differences in the prevalence of overuse injury between the intervention and control groups will be assessed by comparing their mean prevalence (independent T-tests and/or Mann-Whitney test). Secondary analyses will be conducted to compare the onset of acute and overuse injury between the intervention and control groups based on three levels of adherence (low, medium, high).

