**Methods:**

A randomized prospective controlled trial with a follow-up period of one volleyball season will be conducted. Participants will be healthy recreational adult volleyball players (18 years of age or older) practicing volleyball (training and/or match) at least twice a week. The intervention (‘VolleyVeilig’) consists of a warm-up program based on more than 50 distinct exercises (with different variations and levels). The effect of the intervention programme on the occurrence of injuries will be compared to volleyball as usual. Outcome measures will be incidence of acute injury (expressed as number of injuries per 1000 h of play) and prevalence of overuse injuries (expressed as percentage).

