### Objective and hypothesis

The objective of the study is to evaluate the effectiveness of the developed intervention (‘VolleyVeilig’) on the one-season occurrence of finger/wrist, shoulder, knee and ankle injuries among recreational adult volleyball players. Analogous to previous studies about the effect of preventive interventions in volleyball [7] and in other sports [8, 9], the hypothesis of this study is that the developed intervention will lead to a 40% reduction of the number of musculoskeletal injuries over the one-season follow-up in the intervention group by comparison to the control group.

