### Sample size

Analogous to previous studies about the effect of preventive interventions in volleyball [7] and in other sports [8, 9], the assumption is that a 40% injury reduction will be achieved over one season in the intervention group by comparison to the control group. To achieve 80% power with a significance level of 0.05, an injury prevalence estimate of 0.25 in the control group and a loss to follow-up among players of 15% over one season (no multiple cluster randomization), the sample size calculation reveals that 640 volleyball players are needed in the study [4]. Consequently, we will strive to enroll 64 teams (average of 10 players per team) assigned either to the intervention or the control group (equal number of 32 teams in each group). The teams within the intervention and control groups will be matched according to their competition level.

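### The acute injury rate counts all new injuries of the season but only the hours up to the first injury, so the reported incidences come out too high

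*Protocol article*

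**What the plan says.** The abstract of the protocol article names as an outcome the "incidence of acute injury (expressed as number of injuries per 1000 h of play". The Statistical analysis section then gives the formula. The numerator comes from "dividing the number of newly incurred acute injuries (excluding re-injuries) identified during the follow-up by the sum of volleyball exposure". The exposure that forms the denominator is qualified as "total exposure, training exposure and match exposure) in hours until the first injury". The same definition serves total, training and match incidence, each with a 95% confidence interval.

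The comparison between arms is separate: "Differences in the incidence of acute injury between the intervention and control groups will be assessed using cox regression analysis". The section does not say what the event in that model is, and it names no rate ratio formed from the incidences.

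The Objective and hypothesis section expects that the programme "will lead to a 40% reduction of the number of musculoskeletal injuries over the one-season follow-up". Under Exposure and injury monitoring, coaches report each player's participation every two weeks through the season. Players complete the injury questionnaire at the same interval, with follow-up questions on location and recurrence.

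**The concern.** A rate needs events and time at risk from the same window. Here the only limit on the numerator is that re-injuries are dropped. Take a player with an ankle injury in October and a new finger injury in February. That player adds two events but only the hours up to October. The questionnaire runs all season and four body sites are targeted, so such second injuries can be recorded and they meet the numerator as written.

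The effect is to overstate each arm's injuries per 1000 h. The overstatement grows with the injury rate, so it is larger in the arm with more injuries. Because the hypothesis concerns the number of injuries, readers are likely to set the two published rates side by side. That informal ratio would lie further from 1 than the true one, and it need not agree with the Cox result printed beside it.

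**Working it through.** **Inputs.** From the Sample size section: "an injury prevalence estimate of 0.25 in the control group", and the assumption that "a 40% injury reduction will be achieved over one season in the intervention group by comparison to the control group". The article states no value for the incidence itself, so there is no published rate to reproduce.

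**How the plan uses the 0.25.** The sample size shows that it acts as the proportion of players injured over the season. The stated target is "To achieve 80% power with a significance level of 0.05". Comparing 0.25 with 0.6 × 0.25 = 0.15, two-sided (the sidedness is not stated) and with continuity correction, needs 270 players per arm. Allowing for 15% loss, 270 / 0.85 = 317.6, so 318 per arm and 636 in total. At ten players per team this rounds up to 32 teams per arm, or 640, as stated. Without the continuity correction the result is 250 per arm and about 590 in total.

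**Model.** Let new acute injuries occur at a constant rate with mean m per player-season.

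- Proportion with at least one injury: p = 1 − e^(−m), so m = −ln(1 − p).
- Expected injuries per player: m.
- Expected exposure to first injury, with the season set to 1: (1 − e^(−m)) / m.
- Rate as written: m divided by that exposure. This is the true rate m times f(m) = m / (1 − e^(−m)), which exceeds 1 and rises with m.

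**Control risk 0.25, true rate ratio 0.60.**

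- Control: m = −ln(0.75) = 0.2877, and f = 0.2877 / 0.25 = 1.151.
- Intervention: m = 0.6 × 0.2877 = 0.1726, and f = 0.1726 / 0.1585 = 1.089.
- Ratio as written: 0.60 × 1.089 / 1.151 = 0.568, an apparent reduction of 43% instead of 40%.

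Per 1000 control players this is about 288 new injuries, of which 250 are first injuries, over 0.25 / 0.2877 = 0.869 season per player (869 player-seasons). The formula gives 288 / 869 = 0.331 per player-season. Both matched versions give 0.288 (250 / 869 and 288 / 1000).

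**Other control risks (assumed), true ratio 0.60.**

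| Control risk | Control inflation | Intervention inflation | Ratio as written |
|---|---|---|---|
| 0.10 | 5.4% | 3.2% | 0.588 |
| 0.15 | 8.3% | 4.9% | 0.581 |
| 0.25 | 15.1% | 8.9% | 0.568 |

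If the 40% is read as a reduction in risk (0.25 to 0.15), the true rate ratio is 0.565 and the formula gives 0.532. With equal true rates the ratio is 1.00 at every risk in the table.

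**Simulation** (1,000,000 players per arm, control risk 0.25): 0.5675 as written, 0.5997 for first injuries over time to first injury, and 0.5998 for all injuries over all exposure.

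**Variation between players.** With gamma frailty of variance 0.5, 1 and 2 and control risk held at 0.25, the ratio as written stays at 0.568 to 0.569, and control inflation is 15.5% to 16.7%. All injuries over all exposure still gives 0.60. First injuries over time to first injury gives 0.616 to 0.661. The two matched rates then answer different questions and need separate labels.

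**The case against.** The strongest reply is that the authors meant first injuries only. References to new injuries and to exposure ending at the first injury can be read that way, and the formula would then be consistent and suit a Cox model. This is possible. But the article is explicit about what it removes, namely re-injuries, and that exclusion would be redundant if each player could contribute only one injury. As it stands, two analysts could compute two different rates.

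Second, the planned comparison is Cox regression. This stands. If the model uses time to first injury, its hazard ratio and p-value do not depend on the formula. A reader might infer that the trial's test is biased towards the intervention or could produce a false positive. The article does not support that: it plans no rate ratio, and even an informal ratio is unbiased when the true rates are equal.

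Third, the size. A reader might take the top of the range in the Background, 10.7 per 1000 h, and assume 120 h per player. This gives m = 1.284, control inflation of about 78% and a ratio of about 0.48. That scenario does not fit this trial. The 10.7 covers acute and overuse injuries together. It implies that 1 − e^(−1.284), about 72%, of controls are injured, against the plan's 0.25 and the Discussion's expectation that most players stay uninjured. The hours per player are not in the article.

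A reader might also expect differences in injury proneness to worsen the ratio. They do not: at risk 0.25 the ratio hardly moves, and at the high rate the distortion shrinks, to a ratio of 0.51 to 0.54.

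Finally, the 15% is on the high side. The 0.25 is not specific to acute injuries. The model counts every later injury as new, and it returns players at once to full exposure although an acute injury is defined as one that stops activity.

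**Conclusion.** The formula is wrong as written: its numerator and denominator cover different person-time, and it defines a declared outcome. The harm is confined to the reported acute incidences, their confidence intervals, and their agreement with the Cox result.

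Under a constant rate with every later injury counted as new, the overstatement is up to about 15% in controls and 9% in the intervention arm at a risk of 0.25. A true ratio of 0.60 then reads about 0.57. At an assumed acute risk of 0.15 the control inflation is about 8% and the ratio about 0.58. The distortion of the ratio is therefore modest and vanishes when the arms do not differ. That the Cox test is untouched rests on its modelling time to first injury, which is the usual reading but is not stated.

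**What to change.** In the Statistical analysis section, make the two parts match. Define acute incidence as the number of first acute injuries divided by hours of exposure up to the first acute injury, for total, training and match exposure alike. This agrees with a Cox model for time to first injury, and the same sentence can state that event.

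If the number of all new acute injuries is also reported, as the wording of the hypothesis invites, divide it by total exposure over the whole follow-up and label it as a separate measure.

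The cost is one sentence, or two if both rates are reported. No new data are needed, because coaches already report exposure for the whole season.

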### Study design and allocation

A randomized prospective controlled trial with a follow-up period of one volleyball season (September, 2017 – June, 2018) will be conducted (Fig. 1). In The Netherlands, Nevobo organizes its recreational competitions in 4 different geographical regions and recreational teams compete against each other within a geographical region. For practical reasons, the two largest competition regions (geographical regions West and East) will be selected for the study and randomly assigned to an intervention region and a control region. This is done to avoid any contamination and competitive bias within a competition region. The expectation is that coaches might be more inclined to participate if the group allocation and thus the volleyball conditions (training and match) do not differ between teams within a competition region. The need for ethical approval was waived by the Medical Ethics Review Committee of the Academic Medical Center because the Medical Research Involving Human Subjects Act (WMO) does not apply to our study protocol (W17_048#17.065; Amsterdam, The Netherlands). The study protocol is registered in the Dutch Trial Registry (ID: NTR6202).

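### The overuse comparison as written takes 2-week group prevalences as its only replicates, so an independent-samples test treats repeated reports from the same players as independent

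*Protocol article*

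**What the plan says.** All of the recipe stands in the Statistical analysis section of the protocol article. It has three steps.

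1. For each 2-week period, prevalence is obtained by "dividing the number of participants reporting an overuse injury during that period by the total number of respondents during the same period". This gives one number per group per period.
2. Then "mean prevalence (and its 95% CI) will be calculated by dividing all prevalence rates measured every 2 weeks by the number of 2-week periods".
3. Differences between the groups "will be assessed by comparing their mean prevalence (independent T-tests and/or Mann-Whitney test").

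The section on exposure and injury monitoring shows where the reports come from: "Players will be asked every two weeks during the 2017–2018 season to complete the translated and modified Dutch version" of the OSTRC questionnaire. The same section states that "Overuse injury is defined as a non-sudden event gradual in onset sustained by a player due to participation in volleyball".

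No repeated-measures, mixed, GEE or cluster-adjusted method is named for this comparison. The within-player correlation is not given.

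**The concern.** An independent t-test or a Mann-Whitney test needs several independent observations per group. A season-long group mean is a single number, so the test needs replicates, and the only ones the text builds are the period prevalences.

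Those values share their players. If one arm happens to contain more players prone to overuse complaints, all of its period values move up together. The spread of the values around their own mean does not show this, yet that spread is what the test takes as its error term. The standard error is then too small and the p-value too low.

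Overuse prevalence is one of the two outcome measures named in the abstract, and the Discussion ties the results to nationwide implementation. A programme without effect could appear helpful or harmful far more often than the nominal level allows.

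**Working it through.** **Inputs from the article**
- Number of periods T. The season gives a "follow-up period of one volleyball season (September, 2017 – June, 2018"), which is about 20 two-week periods. The Intervention section gives fewer: "The intervention is divided into 6 phases, each lasting 5 to 6 weeks", so 30–36 weeks and 15–18 periods. I use T = 15 and T = 20.
- Players per arm. 456 enrolled (Discussion) gives 228 per arm; the planned 640 (Sample size) gives 320.
- Nominal level: 0.05, taken as two-sided.

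**Assumed, because not given:** the within-player correlation ρ between reports in different periods. Range shown: 0.05 to 0.3.

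**The plan's own figure.** The Sample size section starts "To achieve 80% power with a significance level of 0.05, an injury prevalence estimate of 0.25 in the control group" and adds a 40% reduction and 15% loss. Comparing 0.25 with 0.15, two-sided, with continuity correction, needs 270 per arm. Then 270/0.85 = 317.6, so 318 per arm and 636 in total, against 640 stated. The figure reproduces. It counts each player once, so the calculation has the player as its unit, whereas the overuse comparison supplies only periods.

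**Formula.** Let n be the players per arm, p the prevalence and v = p(1−p)/n. With equal correlation ρ between any two reports of a player and no seasonal change:
- true variance of an arm mean over T periods: v[1 + (T−1)ρ]/T
- variance the test uses, on average: v(1−ρ)/T
- ratio R = [1 + (T−1)ρ]/(1−ρ)

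Both n and p cancel. The null rejection rate is P(|t| > c/√R) on 2T−2 degrees of freedom, where c is the two-sided 5% critical value: 2.048 for T = 15 (28 df) and 2.024 for T = 20 (38 df).

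| T | ρ | R | c/√R | Null rejection |
|---|---|---|---|---|
| 15 | 0 | 1 | 2.048 | 5% |
| 15 | 0.05 | 1.70/0.95 = 1.79 | 1.531 | 14% |
| 15 | 0.1 | 2.40/0.90 = 2.67 | 1.254 | 22% |
| 15 | 0.3 | 5.20/0.70 = 7.43 | 0.752 | 46% |
| 20 | 0 | 1 | 2.024 | 5% |
| 20 | 0.05 | 1.95/0.95 = 2.05 | 1.413 | 17% |
| 20 | 0.1 | 2.90/0.90 = 3.22 | 1.128 | 27% |
| 20 | 0.3 | 6.70/0.70 = 9.57 | 0.654 | 52% |

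**Check by simulation** of binary reports (600 replicates per setting, 15 or 20 periods, prevalence 0.15 or 0.25, no seasonal change):
- Zero correlation: both tests reject in about 4–5%.
- Correlation decaying with time, about 0.45 between adjacent reports: t-test 27–32%.
- All settings with average correlation 0.09–0.57: t-test 23–73%, Mann-Whitney 22–71%. Changing the test does not help.
- 320 players per arm: 25–68%. More players do not help either, as the formula predicts.
- One value per player (share of periods with overuse injury) in a t-test: 3–7%, with no team or region effect.

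**Effect of a shared season.** If prevalence rises and falls alike in both arms, the swing cancels from the difference but adds a variance s² to the scatter that the test uses:

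R = v[1 + (T−1)ρ] / [v(1−ρ) + s²]

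Take a sine-shaped swing of 10 points from peak to trough, T = 20, n = 228 and ρ = 0.1. Then s² = (0.05²/2)(20/19) = 0.00132.
- p = 0.15: v = 0.000559, R = 0.00162/(0.00050 + 0.00132) = 0.89
- p = 0.25: v = 0.000822, R = 0.00238/(0.00074 + 0.00132) = 1.16

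Both are close to 1, so the rate falls to near nominal. Simulations with a 10-point swing and low correlation gave about 4–11%. With the same swing and average correlation 0.27–0.57 they gave 20–41%.

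**The case against.** - **The unit is inferred.** The article never says that the period is the unit of the test. A test on each player's share of affected periods would hold its level at 3–7% without a team effect, and at 8–13% with a modest assumed one. This stands as a limit on wording. But that analysis needs a per-player summary that the article does not contain. The estimator and the test are both named, so this is not simply detail left to an analysis plan.
- **The rate is conditional.** A reader might infer that the false-positive rate is several times 5% whatever the data. The documents do not support that. They give no correlation; at ρ = 0.02 and T = 20 the formula gives R = 1.38/0.98 = 1.41 and about 10%. A large shared swing can bring the rate near 5%, and random non-response dilutes the effect: in one setting with average correlation 0.28, 60% response lowered 53% to 36%. Still, most plausible settings are inflated, and an error rate that is right only when two faults cancel does not make the test valid.
- **The confidence interval.** A reader might infer that the planned 95% CI for mean prevalence is wrong as well. The article says how the mean is formed but not how its interval is. The fault follows only if the interval is computed from between-period scatter; a bootstrap over players would avoid it.
- **The design.** Each arm is one competition region (Study design and allocation). A player-level model does not remove this confounding. That is true, but it is no reason to keep the present test.

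**Conclusion.** Wrong as written. The only replicates that the article defines for the overuse comparison are 15 to 20 dependent period prevalences per arm, and both named tests assume independent observations. For a within-player correlation of 0.05 to 0.3, null rejection is about 14–46% with 15 periods and 17–52% with 20, against 5%.

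These rates assume equal correlation between periods, no seasonal change, and no team or region effect. The exception is a shared swing of about 10 points with low correlation (about 4–11%). The correlation itself is an assumption, but a value near zero would be surprising for a gradual-onset condition tracked in the same players.

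**What to change.** Replace the t-test/Mann-Whitney comparison with an analysis of the player-level report, overuse injury yes or no in each 2-week period:
- GEE or mixed logistic regression with effects for arm and period, and the age and gender adjustment already foreseen for the acute outcome;
- correlation within player, and clustering of players by team;
- the model-based difference in mean prevalence with its 95% CI as the reported result;
- period prevalences kept as a descriptive table or curve, with any interval for the mean prevalence taken from the model or from resampling players or teams, not from scatter between periods.

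State next to the result that, with one region per arm, neither this model nor any similar one separates a region effect from the intervention effect, and that the interval leaves out variation between regions.

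The cost is a change of wording and modest analysis work. The fortnightly player reports are already being collected, so no new data are needed. The interval will be wider and less favourable than one based on scatter between periods.
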